#### Assignment of intervention

Participants will be randomly assigned to three interventions groups 1) the experimental group (personalized exercise using study-app); 2) an active control (counseling concerning standard WHO guidelines); and 3) a control group (no intervention). We will enroll 300 participants.

### Intervention

As shown in in the study flow chart (Fig. 1), the intervention will last 8 weeks. Following informed consent forms and collection of preliminary demographic and clinical data (T0), all participants will undergo fitness assessment by the test app before the intervention (T1), in which their fitness (Low or High) will be determined. They will then be re-assessed after 4 weeks (T2), after 8 weeks (T3), and after 12 weeks (follow-up T4). The testers will be well trained research assistants who will use their own mobile phone for the testing.

**Fig. 1 Fig1:**
[figure not shown]
Flow chart of study design

### Intervention groups

***The experimental group (n = 100):*** participants will receive their personalized exercise program based upon the assessment of their performance level in each of the following fitness component: balance, flexibility, strength. Following the pilot study [17], and according to evidence supporting the advantages of exercising > 3 times/week [1], they will be instructed to exercise five times/week. Their videoed exercise program will be delivered to their personal mobile phone. An example of exercise as displayed on the mobile phone is presented in Fig. 2. The exercises are grouped into three target categories: 1) balance and lower body exercises, 2) upper body flexibility exercises, and 3) upper body strength exercises. Each exercise was coded according to target categories, and two levels of difficulty based on two levels of fitness: A (simple level) and B (advanced). Examples of typical exercises for each of the three motor components, for both levels of difficulty are demonstrated in our pilot study [17].
***An active control group (n = 100):*** participants will be asked, on individual basis, to exercise according to the official general guidelines published by the World Health Organization [1]. More specifically, they will be asked: 1) To perform leisure type aerobic exercise for 150-300 min or intensive exercise for 75-150 min. Per week. Examples such as walking, jogging, riding bicycle will be given; 2) In addition, they will be asked to perform ≥three times a week multicomponent physical activity that emphasizes functional balance and strength training at moderate or greater intensity. They will get the following examples of balance exercises: standing on toes, one leg-stance, walking while lifting knee, walking backwards, side walk while bending and extending knees. Examples of strength exercise: in standing position - lifting leg to side (abduction), extending straight leg backwards, lifting straight leg forward, sit and stand, standing against wall: pushing body with hands to wall, lifting arms to side – possibly with dumbbells.
***A control group (n = 100***): participants will be advised to continue their normal routine, and if interested, will be able use the smart app exercise program after the completion of the study.

**Fig. 2 Fig2:**
[figure not shown]
An example of exercise for arms flexibility for level A and B as displayed on phone

### Matching fitness level with exercise prescription (artificial intelligence)

The data collected in the pilot study, served as a baseline for big-data collection and for subsequent use of artificial intelligence (AI). Based on this preliminary data collection and the AI, the system will determine the level of fitness (Low or High) of participants in the present study, and subsequently the level of difficulty of exercise to be assigned (A or B) for each fitness component. Figure 3 demonstrates an example of a study participant’s unique fitness profile based upon the digital markers, graphically displayed alongside the average profile for the complete study sample. The prescribed exercise, generated automatically following the baseline testing session (T1), will be directly delivered, via the mobile phone, to the participants of the personalized exercise (experimental) group, and adapted based on the scores of T2, if needed (see flow chart in Fig. 1). Prescribed exercise will be delivered to the control groups, upon request, after the termination of the intervention. As new data is obtained, the ability of the program to generate personalized exercise program will be further refined.

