### Eligibility, inclusion and exclusion criteria

Healthy volunteers aged ≥65 years, males and females are eligible, who for inclusion must meet all the following criteria: 1) home or independent living; 2) fluent Hebrew speakers; 3) able to walk independently without help from another person; 4) functionally independent in dressing, toileting, grooming, washing, eating; 5) a smartphone user.

Exclusion criteria are ≥1 positive from the following: 1) Cognitive decline < 3/5 on Mini-Cog Score [18]; 2) Any hospitalization (> 24 h) or at least one Emergency Room referral in previous 12 months; due to unstable heart disease (congestive heart disease/rhythm disorder/ischemic heart disease/valvular heart disease) or neurological disease including balance or dizziness (cerebrovascular disease, vestibular disease, progressive neurological disease affecting gait or balance). (Information by self-report on direct questioning); 3) High risk of falling, as assessed by any positive answer to one of the 3 validated questions previously used in community-based exercise intervention and fall prevention studies [19]: a) Have you fallen over twice or more in the last year?; b) Have you fallen and hurt yourself in the last year?; c) Are you afraid that you might fall because of balance or walking problems?; 4) Unwilling to provide consent.

All participants will undergo assessment by the study physician in order to assess eligibility. The study physician will also gain informed signed consent, whereupon preliminary background data will be collected by trained research assistants. All participants who during the study trial experience an event listed in the exclusion criteria will be asked to discontinue the trial. Similarly, participants will be free to leave the trial at any time. In addition, participants will be asked to refrain from initiating new additional exercise programs during the study period.

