### Primary outcomes

The primary outcome measures are the changes in the following motor components, all of which are included in the remote fitness assessment (see Table 1 and Additional file 1): static balance (postural control in standing), dynamic balance (postural control while moving), strength (muscle endurance) of upper and lower extremities, and flexibility (range of motion in upper and lower body). All outcomes will be measured among all participants at baseline (T1), at 4 weeks (mid-intervention) (T2), at 8 weeks (end of intervention) (T3), at 12 weeks (one-month post intervention) (T4).

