#### Data analysis

The following 2-ways ANOVAs with repeated measures (3 treatment groups X 4 times measurements – T1-T4) will be conducted for each digital marker as follows:For all participantsSeparately for each of the following four subgroups: young women and young men (age 65-74), and old women and old men (age 75+).Separately for each of the two levels of fitness (Low and High) for each component. For example: low level of balance performance in the experimental group (personalized) compared to low level of balance in the control groups.Bonferroni will be used for post-hoc analyses, and False Discovery Rate [27] will be used to account for multiple comparisons.

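### The protocol gives two different access times for controls to use the app programme, and the earlier one leaves the week-12 (T4) comparison open to dilution

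*Protocol article*

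**What the plan says.** Two sections of the protocol article say when controls may have the app programme.

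- **Matching fitness level with exercise prescription:** "Prescribed exercise will be delivered to the control groups, upon request, after the termination of the intervention". The plural covers both the active and the passive control arm.
- **Intervention groups**, in the paragraph on the passive control arm: interested participants "will be able use the smart app exercise program after the completion of the study". The active-control paragraph says nothing about later access.

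The timeline separates these two moments. The Intervention section states that "the intervention will last 8 weeks", and it schedules a follow-up assessment at week 12. Primary outcomes labels the last two assessments "at 8 weeks (end of intervention) (T3), at 12 weeks (one-month post intervention) (T4".

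Two other statements bear on the point. Under Eligibility, "participants will be asked to refrain from initiating new additional exercise programs during the study period"; the article does not define that period. Under Data analysis, "2-ways ANOVAs with repeated measures (3 treatment groups X 4 times measurements – T1-T4) will be conducted for each digital marker", so T4 enters the main model for every marker.

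**The concern.** The end of the intervention and the end of the study are four weeks apart, and the two access statements are tied to different ends. They also differ on who is covered: both control arms in one, the passive arm in the other.

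Staff who follow the looser statement could give controls the experimental programme between T3 and T4. The request not to start new exercise programmes would then sit badly with an offer of exactly that, if the study period runs to T4.

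At stake is the T4 contrast, and the group-by-time test so far as it draws on T4. Controls who take up the programme early would probably narrow the T4 difference. Because access is on request, those who take it up would be self-selected, and uptake could differ between the two control arms. Exposure before T4 cannot be undone afterwards.

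**Working it through.** **1. Timeline.**

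| Access rule | Earliest access | Possible exposure before T4 (week 12) |
|---|---|---|
| After the intervention ends (both control arms) | week 8 | 12 − 8 = 4 weeks |
| After the study is complete (passive arm) | after week 12 | 0 weeks |

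**2. Who is exposed.** The active-control arm (n = 100) is governed only by the first rule. The passive arm (n = 100) falls under both, and is exposed before T4 only if the first is followed over the second.

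**3. The plan's own power figure, as background.** The plan states 86% power for group differences at f = 0.15 with 100 per arm. Using the noncentral F for the between-group effect in a repeated-measures design, λ = f²·N·m / (1 + (m − 1)ρ), with N = 300, df = 2 and 297, and assumed α = 0.05:

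- m = 4, ρ = 0.5: λ = 0.0225 × 300 × 4 / 2.5 = 10.8, power 84.2%
- m = 3, ρ = 0.4: λ = 0.0225 × 300 × 3 / 1.8 = 11.25, power 85.7%

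Both are within 2 points of the stated figure. The plan states neither ρ nor α. It also gives no power for the T4 contrast alone, so the point does not rest on this figure.

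**4. Dilution at T4.** Let u be the share of a control arm that starts the programme after T3. Let g be the share of the full effect those participants gain by T4, and d the undiluted T4 difference in SD units. If the experimental arm still holds its full effect at T4, then

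d(T4) = d × (1 − u·g), and power ≈ Φ( d(T4)·√(n/2) − 1.96 ), with n = 100 per arm and two-sided α = 0.05.

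The document gives none of u, g or d; all are assumed here.

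| u | g | d(T4) if d = 0.5 | Power | d(T4) if d = 0.3 | Power |
|---|---|---|---|---|---|
| 0 | – | 0.500 | 94.2% | 0.300 | 56.4% |
| 10% | 0.5 | 0.475 | 91.9% | 0.285 | 52.2% |
| 25% | 0.5 | 0.438 | 87.2% | 0.263 | 45.9% |
| 25% | 1 | 0.375 | 75.5% | 0.225 | 35.6% |
| 50% | 1 | 0.250 | 42.4% | 0.150 | 18.4% |

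Example, u = 25% and g = 0.5: 0.5 × (1 − 0.125) = 0.4375; Φ(0.4375 × 7.071 − 1.96) = Φ(1.134) = 87.2%.

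**5. Sensitivity to retention.** If the experimental arm keeps only a fraction r of its effect at T4, the proportional loss is u·g / r. For u = 30% and g = 0.5 the loss is 15% when r = 1, and 0.15 / 0.5 = 30% when r = 0.5. For u = 60% and g = 0.5 it is 30% and 60%. No single percentage can be defended.

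**The case against.** The strongest reply is that the statements are compatible. *After* sets only an earliest bound, and week 12 is also after the intervention has ended. If access opens once T4 is done, both access statements and the request about new exercise programmes are all satisfied. This stands. A reader might infer that the statements cannot all hold, but the wording does not go that far: one is looser than the other and permits an earlier start. The flow chart (Fig. 1) is not shown, so it carries no weight either way.

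A reader might also infer that up to 200 controls would be exposed, or that T4 is contaminated. The first requires setting aside the explicit statement for the passive arm. The second requires controls actually to ask for the programme between T3 and T4, and the request about new exercise programmes may restrain that.

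The stated objective is the 8-week programme, and the end-of-intervention comparison at T3 is untouched. Nor was T4 ever a pure measure of retention: nothing says that experimental participants stop at week 8, and the adherence section collects session counts for the preceding four weeks at T4. These points also stand, and they limit the size of the concern.

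Finally, a reader might infer that T4 must leave the group-by-time test. It need not. Later access does not undo randomisation. An as-randomised T4 comparison stays valid for a delayed-access question, though diluted as a comparison with untreated or guideline-only controls.

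What the reply does not remove is the mismatch. Reading the end of the intervention loosely as the end of the study conflicts with the article's own labels for T3 and T4.

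**Conclusion.** The mismatch is real and follows from the article's own timeline. As written, it permits up to four weeks of the experimental programme before T4, clearly for the active-control arm and, depending on which statement is followed, for the passive arm. T4 is a primary-outcome time and a level of the main ANOVA, so that contrast is open to dilution.

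Whether dilution occurs, and how much, is unknown. In the illustration with d = 0.5 it is modest at low uptake and half gain (94% to 92% or 87%). The steep losses need full gain within four weeks (76% at 25% uptake, 42% at 50%). All of these figures rest on assumed values and on full retention of the effect in the experimental arm; partial retention would make the proportional loss larger. Comparisons confined to T1–T3 are unaffected. This calls for a clarification of the plan and does not invalidate the trial.

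**What to change.** Reconcile the Eligibility, Intervention groups and Matching fitness level sections to one access time for both control arms, stated relative to each participant's T4 visit. Say also whether the study period in the request about new exercise programmes runs to T4. The T4 comparison is free of this dilution only if access follows that visit.

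If any access before T4 is kept, do two things:

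- Record app use by control participants. The adherence section describes automatic logging for the experimental group only.
- Interpret the as-randomised T4 comparison as one in which controls had delayed access. T4 can stay in the analysis.

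The cost is one sentence in the protocol and, if access is placed after T4, a wait of at most four weeks for interested controls. Control-arm logging is needed only if earlier access is kept.

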**Fig. 3 Fig3:**
[figure not shown]
An example of a study participant’s unique fitness profile for balance, flexibility and strength

### Strategies to improve and monitor adherence

All participants from the experimental and active control groups will receive personal tutoring regarding his/her exercise program – personalized for the experimental group and general guidelines for the active control group. Participants in the experimental group will get specific guidance how to use their phone for watching their personalized program, and practice accordingly. In addition, they will get a small stand to place the phone in a viewable spot while exercising. Adherence to the programs will be monitored by a) Weekly phone calls to all participants. Participants in the experimental and active control groups will be inquired about difficulties or any comments they have regarding their exercise routine. In T2, T3 and T4 (every 4 weeks) they will be asked to report the average number of exercise sessions spent weekly in the previous 4 weeks. The passive control group will be informed in which week they are in the study, and when is the next fitness test due to occur.; b). The number of minutes spent using the study-app for exercising in the experimental group (the personalized exercise group) will be automatically recorded each time the smart-app exercise program is operated by participants in the intervention group.

### Guidelines for safety

Participants in all groups will be instructed how to act in case of any medical problem arising during the study (see ‘Ethics approval and consent to participate’ in administrative information). Specifically, the experimental (personalized exercise) group will be asked to watch two films delivered to their mobile phone prior to starting the exercise program, participants (see [17]), which will include the following safety rules: “wear comfortable clothes”, “exercise bare foot or wear non-slip socks”, “find a quiet room at home with a place to put an exercise mattress, with an empty wall, and importantly – with a stable chair with back rest”, “don’t exercise if you have pains (greater than 3 on a 1-10 scale)”, “in knees and hands position you can put a mattress under your knees”, “block incoming calls to your phone while you use it for exercising”, “full safety comes first”, “if you feel unsafe, skip the exercise, or stop the training session” “stop if you feel dizzy”. In addition, since some exercises are performed on a mattress, a short film will be shown demonstrating how to get down and up from mattress. The active-control (general guidelines) group will be advised to wear comfortable clothes for exercising, to use comfortable tennis shoes for the aerobic exercise, and tennis shoes or bare foot for the strength and balance exercise, to take safety precautions for fall prevention, and to stop exercising if feels unsafe, or if has pain. Comprehensive insurance will cover the possibility of any medical complications incurred during the study, and the potential need for compensation.

## Measurements

### Remote fitness assessment tool

We will use standard movement performance tests selected by experts and incorporated into the smartphone application (EncephaLog™) developed by Montfort Brain Monitor LTD, utilizing the standard smartphone sensors - accelerometers and gyroscopes. The assessment will include 10 performance tests, operationalized to generate a total of 42 digital markers (see Table 1 and Additional file 1). Briefly, the 10 performance tests assess the following fitness components: static balance, dynamic balance, leg strength, upper body flexibility, and upper extremities strength. Raw data will be uploaded to the remote pooled databank. An example showing graphical demonstration of the raw data collection for the “one-leg stance” is presented in Fig. 4.

**Table 1 Tab1:** Outcome measures

Fitness Components	Tests	Digital Markers	Good performance
Static balance	^a^One-leg stance 10 s.	For each test: average acceleration (m/sec^2^) and angular velocity (radians/sec), in different directions.	*Lower scores – lower sway*
	^a^Tandem stance 20 s.		
Dynamic balance	Tandem walk: 10 steps forwards		
	Tandem walk: 10 steps backwards		
Legs strength	Sit-to-stand 10 rep.	Total time (sec.) and average duration for each rep.	*Shorter duration*
Upper body flexibility	^a^Torso rotation	Angle	*Increased angle - a greater range of motion*
	^a^Arm flexion		
	^a^Arm extension		
Upper extremities strength	^ab^Lifting arm forward 20 rep.	Average duration (sec.)	*Shorter duration*
	^ab^Lifting arm to side 20 rep.		

^a^For left and right separately

^b^with 0.5 kg for women and 1 kg for men

**Fig. 4 Fig4:**
[figure not shown]
Graphical demonstration of raw data generated by smartphone accelerometer (Acc) and gyroscope (Gyro) for leg-stance (one of the authors is the demonstrator). Note. ML – Medio-lateral, from side to side; AP – Anterior-Posterior, forward and backward; SI – Superior-inferior, − up and down

### Additional data

Preliminary background data, collected at interview at T0 will include: Sociodemographic data; Self-reported medical diagnoses and health related variables; Frailty Index [20]; Habitual physical activity (average time spent weekly for aerobic/non-aerobic exercise, daily physical activities, and sedentary time); Mini-Cog test validated Hebrew version [18]; and Geriatric depression score (short 5 item validated Hebrew version) [21].

In addition, the following data will be collected at throughout the study at T1-T4: A modified version of the Flanker Task [22] assessing information processing in visual search (cognition), and the Profiles of Mood State (POMS) [23] validated Hebrew version of the scale [24], consisting of positive and negative feelings felt in previous week.

The sociodemographic, physical activity mood and cognition data be collected by the research assistants, and all other data by the study physicians. All information will be uploaded directly to the mobile phone of the testers, and automatically remotely delivered to the platform.

#### Data Collection and Management

Each participant will be given a confidential study number, with identification record kept separately from all data by the principal investigators (PIs). Data from smartphone collected throughout the study will be uploaded remotely via the study-app platform (by Montfort Brain Monitor), de-identified using the confidential study number.

Data will be stored and analyzed using Microsoft Azure - authentication and authorization with Microsoft Azure Active Directory (Single security token is valid for 60 min). Participant coding on Montfort’s side is pseudonymized, only the PIs know the participants’ personal details. The data is sent to Montfort servers via Hypertext Transfer Protocol Secure (HTTPS), with 2048 bits Secure Sockets Layer (SSL). Local device data is deleted within 2 days after successful upload. Uploaded data is stored on the server for a minimum of 2 years. Data is accessible by Montfort and by 3 research team members at the Wingate College.

### Primary outcomes

The primary outcome measures are the changes in the following motor components, all of which are included in the remote fitness assessment (see Table 1 and Additional file 1): static balance (postural control in standing), dynamic balance (postural control while moving), strength (muscle endurance) of upper and lower extremities, and flexibility (range of motion in upper and lower body). All outcomes will be measured among all participants at baseline (T1), at 4 weeks (mid-intervention) (T2), at 8 weeks (end of intervention) (T3), at 12 weeks (one-month post intervention) (T4).

### Secondary outcomes

Adherence to the exercise programs and changes in feelings and cognition will be compared between the different study groups. In addition, age (65-74 vs 75+) and gender differences in the changes in the primary outcomes will be examined, as well as levels of fitness (Low vs High).

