### Sample size and power analysis

Statistical power was calculated using G * Power [26]. Based on the analysis, 100 participants in each of the 3 treatment groups (experimental, active control, control) enable detecting group differences in statistical power of 86% for a small effect size (Cohen’s f = .15), and in statistical power of 99% for a moderate and high effect sizes (Cohen’s f = .25, .40 respectively). In addition, the statistical power for detecting differences between repeated measures, and in the interaction between groups in the repeated measures is higher than 99% in the moderate effect size as well as in the high effect size.

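### Low/High fitness is set from the same T1 assessment that serves as baseline, so regression to the mean biases Low-vs-High comparisons of change and time effects within a level, but not arm contrasts.

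*Protocol article*

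**What the plan says.** All references are to the protocol article.

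- **Intervention:** "all participants will undergo fitness assessment by the test app before the intervention (T1), in which their fitness (Low or High) will be determined". One occasion is described, with no repeat baseline reading.
- **Matching fitness level with exercise prescription:** "the system will determine the level of fitness (Low or High) of participants in the present study", component by component, drawing on pilot data and AI. No numerical cut is given. The same session drives the prescription: "The prescribed exercise, generated automatically following the baseline testing session (T1").
- **Primary outcomes:** "The primary outcome measures are the changes in the following motor components", and "All outcomes will be measured among all participants at baseline (T1") and at the three later visits. T1 is therefore the starting point of every change.
- **Secondary outcomes:** after age and gender, "differences in the changes in the primary outcomes will be examined, as well as levels of fitness (Low vs High").
- **Data analysis:** a three-arm by four-time repeated-measures ANOVA for each digital marker, with T1 as one of the four times. It is run on everyone, by age and gender subgroup, and "Separately for each of the two levels of fitness (Low and High) for each component". The worked example compares arms within the low balance level. Bonferroni is named for post-hoc tests and False Discovery Rate for multiplicity.

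**The concern.** A T1 reading is partly the person's true level and partly that day's error. Participants who fall below a cut on T1 have, on average, an unfavourable error that day, and those above it a favourable one. The error does not carry over to later visits, so the Low group drifts up in performance and the High group drifts down with no real change. For sway and duration markers, where Table 1 scores lower as better, the raw sign is reversed.

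Age and gender do not share the problem, because neither is measured by the outcome; fitness level is. The planned multiplicity corrections do not help either. They control chance findings, whereas this is a systematic shift in the same direction across markers.

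A finding that Low participants improve, and improve more than High ones, could be taken as support for tailoring by fitness level when no programme works.

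**Working it through.** The plan gives no figure for this effect, so there is none to reproduce.

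**Inputs from the article:** 300 participants, 100 per arm; level set at T1; change measured from T1; levels set per component, analyses run per marker.

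**Assumptions, because the article is silent:** each marker has SD 1; equal correlation r between any two visits, 0.6 to 0.9; a median cut; no effect in any arm; tests at 0.05, unadjusted.

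**1. Cut on the analysed marker.** The mean of a standard normal below its median is -0.798, so the expected change is

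shift in Low = (1 - r) × 0.798, and the negative of this in High.

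| r | Shift per level (SD) | Low minus High (SD) |
|---|---|---|
| 0.6 | 0.4 × 0.798 = 0.32 | 0.64 |
| 0.7 | 0.3 × 0.798 = 0.24 | 0.48 |
| 0.8 | 0.2 × 0.798 = 0.16 | 0.32 |
| 0.9 | 0.1 × 0.798 = 0.08 | 0.16 |

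In simulation, the Low-vs-High test of change is falsely significant in 100%, 100%, over 99% and 86 to 89% of trials respectively. The time effect within Low is significant in about 100%, 98%, 90% and 60%.

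**2. Level averaged over k markers, one of them analysed.** Let c be the correlation between the markers' true scores and s the share of error common to all markers in a session. Then

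shift = 0.798 × (1 - r)[s + (1 - s)/k] / √{[1 + (k - 1)(c·r + s(1 - r))]/k}.

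Take k = 4 and c = 0.5 (both assumed).

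- Independent errors (s = 0), r = 0.6: 0.798 × 0.10/√(1.90/4) = 0.116. At r = 0.9: 0.798 × 0.025/√(2.35/4) = 0.026. Simulated Low-vs-High false positives: about 60% (59 to 62%) at 0.6 and 16 to 17% at 0.9. The Low time effect falls to 32% and 9%.
- Half the error shared (s = 0.5), r = 0.6: 0.798 × 0.25/√(2.5/4) = 0.252 (0.25 to 0.26 in simulation). At r = 0.9: 0.798 × 0.0625/√(2.5/4) = 0.063. False positives: 100% and 69%.

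Moving c between 0.3 and 0.6 changes the r = 0.6 shift only from 0.129 to 0.111 (s = 0), or from 0.273 to 0.244 (s = 0.5).

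**3. What is not affected.** The same shift occurs in every arm at a given level, so it cancels between arms. With the cut on the analysed marker, the simulated false-positive rate for arm comparisons of change within Low is 4.6 to 5.8%. With a true gain of 0.25 SD in the experimental arm and r = 0.8, that arm's Low group appears to gain 0.25 + 0.16 = 0.41 SD and its High group 0.25 - 0.16 = 0.09 SD. Experimental minus control is 0.25 SD in both levels.

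**4. Check of the remedy.** Testing arm by level on the mean of T2-T4 gives 4.4 to 5.3% false positives when analysed as change from T1, and 4.2 to 5.4% with T1 as covariate. These ranges cover all three structures above and r = 0.6 to 0.9.

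**The case against.** **No model has Low vs High as a factor.** The Data analysis section compares arms within a level, and that contrast is clean. The Background hypothesis is likewise between arms, among participants with similar baseline profiles. This stands, and it narrows the point. But Secondary outcomes lists fitness level beside age and gender as a grouping for changes in the primary outcomes, and its plain reading is a comparison of changes between levels. If it means only the same-level arm contrasts, what remains is the time effects and within-arm changes inside each level.

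**The cut is not on the analysed marker.** This also stands. Levels are set per component and analyses are per marker, so the shift is diluted, more so with more markers and less so with few or near-duplicate ones, as for leg strength. A reader might infer that the trial will almost surely report a false Low-fitness advantage. The article does not support that in general: with four independent-error markers the rate ranges from about 60% down to 17%.

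**Stronger readings to avoid.**
- A reader might infer that the randomised comparison is biased. It is not.
- The sample-size section cites "the statistical power for detecting differences between repeated measures", which might suggest that within-level time effects are a powered target. The statement is not made for the levels, and the whole sample is not selected on T1.
- Prescriptions may be adapted after T2, but nothing says that the analysis levels are redefined then.

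**It is a secondary analysis in a condensed article.** True, and which ANOVA terms are interpreted may be settled elsewhere. However, the article itself fixes T1 as classifier, T1 as baseline and change by level as an outcome.

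**Conclusion.** The concern holds in limited form. For any reliability below 1, forming levels on T1 and measuring change from T1 biases the Low-vs-High comparison of changes, and the time effects and within-arm changes inside a level. The direction is certain; the size is not. Under a median cut and r = 0.6 to 0.9, the spurious shift per level is:

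- 0.32 to 0.08 SD with the cut on the analysed marker;
- about 0.12 to 0.03 SD with a four-marker average and independent errors;
- about 0.25 to 0.06 SD with half the error shared within the session.

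The Low-vs-High gap in change is twice each figure. The cut, the reliability, the number of markers per component and the error structure are all assumed. The main between-arm question is untouched, so this is a point to correct in a secondary analysis and not a flaw in the primary comparison.

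**What to change.** In Secondary outcomes and Data analysis, state that:

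1. Low-vs-High differences are tested only as the arm by level by time interaction with T1-T4 as outcomes, or as arm by level on T2-T4 with T1 as covariate. In the second form T1 must be removed from the outcome times, since it cannot be both covariate and outcome.
2. Time main effects, within-arm changes and raw Low-vs-High differences in change, in levels defined from T1, are not interpreted as programme effects.

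The same-level arm contrasts already illustrated in Data analysis stay as they are. No new data or visits are needed, because control participants at each level are already measured.

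The cost is that raw within-level improvement can no longer be presented as a result, and the interaction test has less power. With a median split, a raw Low-vs-High comparison sets 150 against 150, giving a standard error proportional to √(2/150) = 0.115. An experimental-minus-control interaction uses four cells of about 50, giving √(4/50) = 0.283, about 2.4 times as large.
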